### Study outcomes

Primary and secondary endpoints are presents in Table 2. The outcomes of the migraine changes are adjudicated based on the headache diary data. The total days of migraine is defined as migraine frequency per month plus migraine average duration, divided by 24, round up to nearest integral. The definition of responder rate is the percentage of patients who have at least 50% reduction of monthly migraine attacks from their baseline. Other efficacy measures include migraine severity, as assessed by the HIT-6 scale [17], and quality of life alterations, determined by the SF-36v2 questionnaire [18]. These changes would be also analyzed the relationship with a successful PFO closure and residual shunt.

**Table 2 Tab2:** Primary and secondary endpoints

Primary endpoint
Complete cessation of migraine during the follow up.
Secondary efficacy endpoints
Mean reduction of monthly migraine attacks. Mean reduction of monthly migraine days. Responder rate.
Secondary safety endpoints
All-cause mortality. Peripheral embolism. New-onset arrhythmia warranting intervention. New-onset myocardial infarction. Other complications related to PFO closure procedure, device and antiplatelet drugs. Other side effects associated with the drugs used in the study.

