### Sample size and statistical considerations

This was a randomized controlled study with PFO blocking group as the intervention group and drug treatment group as the control group. Migraine frequency (monthly migraine days), improvement in migraine frequency, severity (migraine scale score) and quality of life score were the outcome indicators. According to previous reports, the frequency of migraines treated with medication was 6.5 ± 2.4 days/month. The migraine HIT-6 score was 66.2 ± 5.1; After treatment, the number of migraine attacks per month can be reduced by 25%; SF12 quality of life score increased by 1.2 ± 6.9 points after treatment. The frequency of migraine was expected to decrease by 0.6 days in PFO occlusion group. Migraine scale HIT-6 score decreased by 1.5 points; After treatment, the number of migraine attacks per month can be reduced by 50%; SF12 quality of life score improved by 4.2 points after treatment. The test level was set as bilateral α = 0.05, and the assurance was 80%. PASS 15.0 software was used to calculate the required sample size of 113, 183, 60 and 156 cases in each group based on the above four observation indicators. Taking the maximum sample size and considering 20% of the cases of loss and refusal to visit, the final requirement was 220 cases in the PFO blocking group and 220 cases in the drug treatment group.

The primary endpoints will be analyzed across different analysis sets: Intention-to-Treat, per-protocol, and as-treated, with the primary analysis set being Intention-to-Treat. Categorical variables will be described using rates and composition ratios. Group differences in variables such as migraine termination, sociodemographic factors, migraine incidence rate, changes in migraine characteristics (with or without aura and their changes), effective closure rates, or residual leakage will be compared using the chi-square test. Continuous variables will be characterized based on their data distribution, utilizing means, standard deviations, medians, and interquartile ranges. Group differences in variables such as sociodemographic factors, severity and frequency of migraine attacks, and quality of life scores derived from the SF-36v2 questionnaire will be compared using t-tests or the Wilcoxon test.

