Additional analysis will involve covariance analysis to account for factors significantly influencing the observed indicators. Different centers will be treated as random effects, and generalized linear models will be employed to further control for the potential impact of center effects. Stratified analysis will be performed based on factors such as gender and age. Predefined subgroups will include migraine with or without aura. Survival function estimation will be conducted using the Kaplan–Meier method. Relevant covariates will be controlled for using the Cox proportional hazards model, and truncated data will be analyzed accordingly.

For all analyses, a two-tailed *P* value < 0.05 was used as the criterion for statistical significance. Analyses were performed using SPSS 22 software (IBM Corp., Armonk, NY, USA).

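### One P < 0.05 rule covers every analysis with no testing order, so efficacy claims below the primary endpoint carry no overall error control

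*Protocol article*

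**What the plan says.** Study outcomes, Table 2, names one primary endpoint, "Complete cessation of migraine during the follow up", and three secondary efficacy endpoints: "Mean reduction of monthly migraine attacks. Mean reduction of monthly migraine days. Responder rate". The text of that section adds HIT-6 and SF-36v2 as further efficacy measures.

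Sample size and statistical considerations makes Intention-to-Treat the primary analysis set, beside per-protocol and as-treated sets. It also describes the outcomes differently from Table 2: "Migraine frequency (monthly migraine days), improvement in migraine frequency, severity (migraine scale score) and quality of life score were the outcome indicators". Cessation is not among these four. A sample size is derived for each of them under one setting: "The test level was set as bilateral α = 0.05, and the assurance was 80" per cent.

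The section later provides for further cuts of the data: "Stratified analysis will be performed based on factors such as gender and age. Predefined subgroups will include migraine with or without aura". It ends with the decision rule: "For all analyses, a two-tailed *P* value < 0.05 was used as the criterion for statistical significance". The article gives no order of testing, no division of alpha, and no statement that any analysis is exploratory.

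**The concern.** The rule is an explicit statement that reaches every analysis in the plan. Followed as written, it lets a secondary endpoint, HIT-6, quality of life, a per-protocol result or a stratum be called statistically significant at the full 0.05 after cessation has failed. The sample size text adds to this by giving four non-primary measures their own alpha and power, so a reader could take them as co-equal tests.

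This matters for the trial's purpose. The Background says that none of three earlier randomized trials met its primary endpoint. The Discussion adds that a pooled analysis of two of them was favourable. A missed cessation endpoint accompanied by one nominally significant lower-tier result would leave the question about as open as the trial found it.

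**Working it through.** **Level and sidedness.** The article states no overall error rate across endpoints, so the only figure of its own to reproduce is the governing sample size. Inputs from the sample size section: HIT-6 difference 1.5, SD 5.1, two-sided alpha 0.05, power 80%.

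- Normal approximation: n = 2 × (1.960 + 0.842)² × 5.1² / 1.5² = 181.5, so 182 per group. The t-based calculation gives 182.4, so 183, as stated.
- 183 × 1.2 = 219.6, which gives the stated 220.
- A one-sided 0.05 would give 143.

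So the level really is two-sided 0.05 per test. Only the breadth of the rule is in question.

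**Number of tests.** Table 2 lists three secondary efficacy endpoints (k = 3). Adding HIT-6 and SF-36v2, one score each, gives k = 5.

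**Independent tests.** With no true effect, the chance of at least one P < 0.05 is 1 − 0.95^k:

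- k = 3: 1 − 0.8574 = 14.3%
- k = 5: 1 − 0.7738 = 22.6%

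**Correlated tests, given a non-significant primary.** Attacks, days and responder rate come from the same headache diary, so independence is an upper case. The documents give no correlations, and a common value ρ is assumed here. Write each test statistic as Z = √ρ·U + √(1 − ρ)·E, with U and E independent standard normals. Let p(u) be the probability that |Z| < 1.96 given U = u. The chance of at least one rejection among k measures, given that the primary test did not reject, is

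1 − E[p(U)^(k+1)] / E[p(U)], where E[p(U)] = 0.95.

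| ρ | k = 3 | k = 5 |
|---|---|---|
| 0 | 14.3% | 22.6% |
| 0.3 | 13.1% | 20.1% |
| 0.5 | 11.1% | 16.6% |
| 0.8 | 6.8% | 9.3% |

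**Only results favouring closure.** Let q(u) be the probability that Z < 1.96 given U = u. The formula becomes 1 − E[p(U)·q(U)^k] / E[p(U)]:

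- ρ = 0: 7.3% (k = 3) and 11.9% (k = 5)
- ρ = 0.5: 5.6% and 8.3%
- ρ = 0.8: 3.4% and 4.7%

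**Not counted.** Per-protocol and as-treated sets, separate visits, several SF-36v2 scores, safety endpoints and strata are left out. Each would add tests under the rule as written, but the document does not say how many.

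**The case against.** Four arguments stand against the point.

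1. *This is a condensed article, and multiplicity is normally SAP content.* That is true of silence, and silence alone would be no finding. Here the article fixes a criterion and extends it to all analyses. The sentence can be read as setting only level and sidedness, and a fixed-sequence test also runs each step at 0.05. But nothing in the text points the reader to a sequence, and an SAP that introduced a gate would narrow what is published.

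2. *The outcomes are ranked.* This stands in part. Cessation is the single primary endpoint, the hypothesis in Study design refers to it, and Intention-to-Treat is the primary set. A reader might infer that the trial's overall 5% error is lost. The document does not support that: the primary test keeps its 5%, and only claims below it are affected. The ranking is one of labels and does not govern testing. Sizing a trial on a measure does not by itself make that measure confirmatory, but it does blur the labels.

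3. *The size can be overstated.* A reader might infer about a one-in-five chance of a false efficacy claim after a failed primary. That needs five nearly independent measures and counts harm as well as benefit. At a correlation of 0.5 it is nearer one in six for five measures and one in nine for the three in Table 2. For results favouring closure it is about 8% and 6%. These corrections stand in full.

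4. *Subgroups.* A reader might want to add a figure for the aura, gender and age strata. The document gives no stratum sizes or age cut-point and does not say that each stratum will be tested separately. No such figure is offered.

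**Conclusion.** The point holds in a limited form. The published rule leaves every efficacy claim below the primary without overall error control. With a non-significant primary, the chance of at least one P < 0.05 in either direction is about 11% for the three Table 2 secondary endpoints (7% to 14%) and about 17% for five efficacy measures (9% to 23%). The central values use an assumed correlation of 0.5, and the ranges run from 0.8 to 0. All figures assume no true effect on any endpoint. Chances in favour of closure alone are about half as large. The validity of the primary test is not in doubt, so this should be corrected but does not undermine the main analysis.

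**What to change.** In Sample size and statistical considerations, replace the closing rule with wording to this effect:

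- The confirmatory criterion, two-sided P < 0.05, applies to complete cessation in the Intention-to-Treat set.
- Only if that test is significant are the three Table 2 secondary efficacy endpoints tested, in a stated fixed order or by Holm (smallest P against 0.05/3 = 0.0167, then 0.025, then 0.05), at overall two-sided 0.05.
- If cessation is not significant, those three are reported with nominal 95% confidence intervals and no claim of significance.
- HIT-6, quality of life, per-protocol and as-treated results, the strata and the aura subgroup are supportive or exploratory. Subgroups are judged by a treatment-by-subgroup interaction estimate with its confidence interval.

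The order, or the choice of Holm, should be fixed before outcomes are compared by arm. The sentence listing the four outcome indicators should say that they served the sample size calculation and do not alter the ranking in Table 2.

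The cost is a few sentences, with no more patients or data and no loss of power for the primary. The small downside is that a secondary result cannot be called significant if the primary fails.

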## Discussion

This study is a multicenter, randomized trail evaluating the effectivity of PFO closure in alleviating migraine. Previously, the three RCT set their primary endpoints as complete migraine cessation (MIST, 2008) [16], monthly migraine days reduction (PRIMA, 2016) [15] and responder rate (PREMIUM, 2017) [14]. Although some non-randomized studies suggest the efficacy of PFO closure in migraine relief, none of the aforementioned RCTs achieved their set endpoints. In the 2008 MIST study, patients in the closure group were implanted with the STARFlex Technology device, which has been reported with a higher complication. In addition, a relatively shorter follow up time might also underpower the PFO closure effect. While in the PRIMA and PREMIUM study, both use Amplatzer PFO Occluder and had a 12 months follow up time, but still had an in-neglectable frequency of residual shunt (12% & 11% V.S. 6%). Additionally, small sample sizes might have contributed to these studies not meeting their endpoints. Notably, a pooled analysis of PRIMA and PREMIUM demonstrated a significant mean reduction in monthly migraine days, attacks, and an increase in complete cessation rates in the PFO closure groups [19]. A significant discrepancy between RCTs and retrospective studies might stem from the meticulous screening of patients in RCTs for refractoriness to migraine prevention medication, which may not align with real-world clinical practice. To solve these problems, our SPRING study employs a more recent generation of PFO closure devices and strategy, along with a larger sample size. Unlike previous approaches, we are not mandating preventive medication before closure, aiming to assess if patients can achieve migraine relief post-intervention, thus aligning more closely with the scenario when patients first seek medical advice for migraines.

## Conclusion

This multicenter, randomized trial aims to compare the efficacy and safety of PFO closure versus medication in alleviating migraines. Given the inconclusive evidence from previous RCTs, which failed to reach their primary endpoints, our study is designed to provide a robust evaluation of the effectiveness of these treatments in a real-world setting.

## Data Availability

No datasets were generated or analysed during the current study.
